#### Process evaluation

Participation rate will be calculated. In addition, two focus groups will be conducted with members of the recruitment team, smoking cessation trainers, and study participants. The focus groups will aim to identify the advantages and disadvantages of the intervention barriers and facilitators to recruitment and compliance, and the overall therapeutic experience.

Finally, the number, type, and usage of all implemented environmental interventions will be documented monthly.

### Data management

At each food pantry, all participants will receive an identification number. Identifying information including the participant’s name, address and identification number will be kept separately and locked away from all other data and information. All data will be stored for 10 years. Only the research team will have access to trial data.

All original forms will be sent to the University of Hohenheim and will be entered electronically by trained staff. A subsample of original forms will be double entered by two independent scientists. Non-numeric data will be coded by using predefined standard terminology. Data integrity will be achieved by checking data ranges and valid values.

### Sample size

The required sample size was calculated using the function n4prop in the package CRTSize developed for the program R (version 3.3.2) [47].

In a previous study, the smoking status of users of eight food pantries in Berlin was assessed [11]. The number of participants per food pantry in Berlin was, on average, 56 ± 12 (ranging from 36 to 73) and the number of smokers was, on average, 26 ± 8 (ranging from 19 to 41). A systematic review of recruitment strategies of smoking cessation studies revealed that studies using “active strategies” (i.e. interpersonal contact with the research team or program provider) reached from 47% up to 84% of eligible individuals, with lower participation rates among low-educated populations [48]. Therefore, a participation rate of 50% and a sample size per cluster of *n* = 13 will be assumed.

Based on the results of previous studies [49], cessation rates of 10 and 3% are assumed among participants in the intervention group and the control group, respectively.

Assuming an intra-class correlation coefficient of 0.02, a 5% significance level, and 80% power, 32 clusters are needed to detect an effect (16 in the intervention group and 16 in the control group).

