**Methods / design:**

Before starting the cluster randomised controlled trial, stakeholders will be engaged to adapt a behavioural group counselling program for smoking cessation to the needs of the food pantry users in a pre study. Food pantry users and workers as well as other experts, such as smoking cessation trainers, social workers, and psychologists, will be involved, using the world café technique and telephone interviews and a qualitative thematic analysis for data analysis to design the concept of the intervention program will be applied. In the second phase, the impact of the intervention on the smoking status and on food insecurity will be investigated by a cluster randomised controlled trial. A total of 416 food pantry users across 32 clusters (food pantries) in Berlin, Germany, should be recruited and randomly assigned to either the intervention group or the waiting list control group. The intervention will consist of a behavioural group counselling program for smoking cessation, specially tailored for food pantry users, as well as optional nicotine replacement therapy and the implementation of environmental smoking reduction measures in the food pantries. The primary outcomes 6 months after the treatment will be self-reported continuous smoking abstinence, validated by exhaled carbon monoxide (< 10 ppm of carbon monoxide), and increased food security level (the percentage of participants with an improved food security level).

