## Objectives and hypotheses of the study

The main objective of the study is to investigate the impact of the smoking cessation measures on the smoking prevalence and on food security among food pantry users in Berlin.

The following primary hypotheses will be tested:
The percentage of individuals displaying continuous smoking abstinence 6 months after the treatment will be higher in the intervention condition compared to the control condition.The percentage of participants with an improved food security level 6 months after the treatment will be higher in the intervention condition compared to the control condition.The increased food security level will be mediated by continuous smoking abstinence.

Important secondary objectives include
to assess the impact of the smoking cessation measures on other measures of smoking status (point prevalence of smoking abstinence, the mean number of cigarettes smoked per day) and of food insecurity (the mean number of affirmative responses on the FIES) as well as on the health-related quality of life scores and body-mass-index;to investigate whether possible intervention effects are moderated by demographics (age, gender, migration status, socioeconomic status), the nicotine dependence and time perspective.

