### Statistical analyses

The data will be analysed using the intention-to-treat principle, therefore including all participants irrespective of any dropouts after the baseline assessment. Missing values among the intention-to-treat population will be imputed using the baseline observation carried forward technique.

The mean, standard deviation, minimum and maximum will be given for continuous variables. Frequencies will be given for categorical variables.

To investigate differences between the intervention and the control group, independent t-tests for continuous variables and chi-square tests for categorical variables will be used. To test hypotheses 1 and 2, differences in the prolonged smoking abstinence and food insecurity improvement (the percentage of participants with an improved food security level) between the intervention and control group will be investigated using the chi-square test adjusted for intraclass correlation within clusters [50]. To account for the nesting of participants within the food pantry, mixed models with the logit link function will be used to predict cessation and food security improvement. To test hypothesis 3, a structural equation model will be used [51]. This identifies if the intervention condition predicts smoking cessation (path A), if smoking cessation predicts improvement in food security level (path B), if the intervention condition predicts the improvement in food security level (path C), and if the impact of the intervention condition on the improved food security level will be attenuated when controlling for smoking cessation.

Secondary outcomes will be analyzed accordingly.

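### The 5% significance level has no stated sidedness: 32 clusters fit an undeclared one-sided test, while the planned chi-square test, two-sided as ordinarily used, has about 72–77% power rather than 80%

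*Protocol article*

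**What the plan says.** The Sample size section of the protocol article takes its effect from earlier studies: "cessation rates of 10 and 3% are assumed among participants in the intervention group and the control group, respectively". For cluster size, "a participation rate of 50% and a sample size per cluster of *n* = 13 will be assumed". It then concludes: "Assuming an intra-class correlation coefficient of 0.02, a 5% significance level, and 80% power, 32 clusters are needed to detect an effect", that is, 16 per arm. The Abstract carries this forward: "A total of 416 food pantry users across 32 clusters (food pantries) in Berlin". The calculation is attributed to the n4prop function of the R package CRTSize, without the options used.

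The Statistical analyses section says that differences in prolonged abstinence and in food security improvement "will be investigated using the chi-square test adjusted for intraclass correlation within clusters". It gives no sidedness for that test. The Objectives and hypotheses section words the first two hypotheses directionally: the percentage "will be higher in the intervention condition compared to the control condition".

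**The concern.** A 5% significance level with no qualifier is ordinarily read as two-sided. A chi-square test compared with its usual 5% critical value is two-sided too, because it squares the difference and rejects in either direction. Under that reading the stated inputs do not lead to 32 clusters at 80% power.

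This is the only power calculation in the article, and it supports a primary outcome. If the sample size rests on a one-sided test and the analysis is two-sided, the stated power does not belong to the planned analysis. A null result on smoking abstinence would be read as coming from a trial with a 20% type II risk, when the risk under the assumed effect is about 23–28%.

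**Working it through.** **Inputs.** From the Sample size section: p1 = 0.10, p2 = 0.03, m = 13 per cluster, intraclass correlation 0.02, significance level 5%, power 80%, k = 16 clusters per arm. The 1:1 allocation is in the section on recruitment of the food pantries and randomisation. Sidedness is stated nowhere, so both versions are run.

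**Common quantities.**
- Design effect: 1 + (13 − 1) × 0.02 = 1.24.
- Sum of variances: 0.10 × 0.90 + 0.03 × 0.97 = 0.1191.
- Clusters per arm: k = (c_α + c_β)² × V, with V = 0.1191 × 1.24 / (13 × 0.07²) = 2.318.

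**Reproducing the plan's figure (one-sided 5%).**
- Normal quantiles: (1.645 + 0.842)² × 2.318 = 14.3, so 15 per arm and 30 clusters.
- t quantiles, iterated on 2(k − 1) degrees of freedom: 15.1, so 16 per arm and **32 clusters**. This matches the plan with the stated intraclass correlation kept.
- Power at 16 per arm: 82.2% (noncentral t, 30 df), 83.3% (pooled z), 83.7% (unpooled z).

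**The same inputs, two-sided 5%.**
- Normal quantiles: (1.960 + 0.842)² × 2.318 = 18.2, so 19 per arm and 38 clusters (38 × 13 = 494 participants).
- t quantiles, iterated: 19.2, so 20 per arm and 40 clusters (40 × 13 = 520 participants).
- Arcsine formula: 17.2, so 18 per arm and 36 clusters.
- Continuity-corrected formula: 21.2, so 22 per arm and 44 clusters.

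**Two-sided power at 16 clusters of 13 per arm.** There are 16 × 13 = 208 participants per arm, an effective 208 / 1.24 = 167.7. The standard error is √(0.1191 × 1.24 / 208) = 0.02665, and 0.07 / 0.02665 = 2.627.

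| Method | Two-sided power at 32 clusters |
|---|---|
| Noncentral t, 30 df | 72.0% |
| Pooled z | 74.1% |
| Unpooled z: Φ(2.627 − 1.960) | 74.8% |
| Arcsine | 77.2% |
| Beta-binomial simulation, adjusted chi-square with estimated intraclass correlation, F(1,30) reference | about 73–74% |
| Same simulation, chi-square reference | about 76–77% |

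A further simulation that treated the design effect as known gave 77.6%, the highest figure obtained. No two-sided method tried reached 80% at 32 clusters with the intraclass correlation at 0.02.

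**The case against.** The strongest defence is that 32 is not a miscalculation. Sidedness is not among the stated inputs, the hypotheses are directional, and a one-sided 5% calculation with t quantiles returns exactly 16 per arm with more than 80% power. A chi-square test on one degree of freedom can also be used directionally through its signed root. And for the planned test with its chi-square reference, the two-sided shortfall is only about 3–4 points.

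Most of this stands, and it limits the finding. A reader might infer that the sample size contains an arithmetic error, or that the protocol's own inputs contradict its 80%. The documents do not support that, because the two-sided figures need an input the protocol does not give. A reader might also infer that the design effect was left out, since a two-sided t-quantile calculation with zero intraclass correlation gives 15.7 and also rounds to 16. Nothing in the article points to that, and a route that keeps the stated 0.02 already fits. That a one-sided option was used is itself an inference from the match, since the software options are not reported.

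The defence does not remove the problem. Directional wording states what is expected; it does not set a one-sided rejection region. No section declares a one-sided test, and the named primary test is two-sided in ordinary use. If the sample size was one-sided, the sample size and analysis sections assume different tests. Nor is this a detail that an article may leave to a fuller document: it prints a specific number, power and test, and they fit together only if an unstated option is added.

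**Conclusion.** The concern holds in this form: the significance level is given without sidedness, 32 clusters match a one-sided 5% calculation that is declared nowhere, and the stated 80% does not hold for the planned chi-square test as ordinarily used. On the two-sided basis, power at 32 clusters is about 72–77% depending on method, about 75% by the standard normal formula. The shortfall is about 3–8 percentage points, and the type II risk is about 23–28% rather than 20%. By the standard formula, 80% power would need about 38–40 clusters.

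This rests on the protocol's assumed rates, an intraclass correlation of 0.02, 13 analysed participants in every cluster, and the ordinary two-sided use of the chi-square test. If a one-sided 5% test was intended, 32 clusters are enough under the same assumptions (about 82–84%), and the defect is that the plan does not say so.

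**What to change.** State the sidedness, and make the Sample size and Statistical analyses sections agree, in one of two ways.

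1. **Two-sided.** Say that the adjusted chi-square test is two-sided at 5%. Restate the power of 32 clusters and 416 participants for 10% vs 3% and intraclass correlation 0.02 as about 72–77% (about 75% by the standard normal formula), naming the method.
2. **One-sided.** Declare a one-sided 5% test in both sections, justify it, and say how the chi-square test will be applied directionally.

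In either case, report the n4prop options used so that the figure can be reproduced.

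The change takes one paragraph. No extra pantries are required to make the statement correct, which matters because the Strengths and limitations section already calls recruiting 32 ambitious. On the two-sided option the cost is a less favourable stated power; on the one-sided option it is having to defend that choice.

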### Statistical analyses

The data will be analysed using the intention-to-treat principle, therefore including all participants irrespective of any dropouts after the baseline assessment. Missing values among the intention-to-treat population will be imputed using the baseline observation carried forward technique.

The mean, standard deviation, minimum and maximum will be given for continuous variables. Frequencies will be given for categorical variables.

To investigate differences between the intervention and the control group, independent t-tests for continuous variables and chi-square tests for categorical variables will be used. To test hypotheses 1 and 2, differences in the prolonged smoking abstinence and food insecurity improvement (the percentage of participants with an improved food security level) between the intervention and control group will be investigated using the chi-square test adjusted for intraclass correlation within clusters [50]. To account for the nesting of participants within the food pantry, mixed models with the logit link function will be used to predict cessation and food security improvement. To test hypothesis 3, a structural equation model will be used [51]. This identifies if the intervention condition predicts smoking cessation (path A), if smoking cessation predicts improvement in food security level (path B), if the intervention condition predicts the improvement in food security level (path C), and if the impact of the intervention condition on the improved food security level will be attenuated when controlling for smoking cessation.

Secondary outcomes will be analyzed accordingly.

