### Study population

The study population will include users of any of the participating food pantries who reported smoking at least one cigarette or cigarillo per day. Participants must be at least 18 years old and able to sufficiently understand and speak German. Exclusion criteria includes non-smokers and individuals who smoke less than daily as well as individuals who do not use any of the participating food pantries. In addition, individuals who are 17 years of age or less, are unable to understand and speak German, or are illiterate, will also be excluded. Finally, individuals who only use e-cigarettes or tobacco heating systems will be excluded, since the impact of the original “Rauchfrei” program on this form of tobacco consumption is currently unknown.

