#### Study procedure

While food pantry users are waiting in line to enter the room where the food is distributed, trained study staff will screen them for inclusion into the study using a checklist. Food pantry users willing to participate will be informed about the aim, the procedure of the study, and data protection measures, by a printed study information sheet. Individuals who are willing to participate will be asked to provide their name and address on a separate form and to complete the informed consent form as well as the questionnaire (t0). Exhaled carbon monoxide will also be measured. To secure blinding during the baseline data assessment, participants will be informed about the allocation of their food pantry on their next visit to the pantry (usually 1 week later) by the project coordinator.

One and 6 months after the intervention, follow up assessments will be conducted by trained staff. Again, participants will be assessed while waiting in line at the food pantry. Each food pantry will be visited twice. Participants who cannot be reached at the food pantry will receive the follow-up questionnaires by post.

Among all participants who complete the follow-up questionnaires, 50 €20 vouchers for either an electronics store or a clothing store will be raffled, irrespective of the participants’ smoking status.

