#### Outcomes

Primary outcomes are continuous smoking abstinence (yes or no; the percentage of participants with continuous smoking abstinence) and increased food security level (the percentage of participants with an improved food security level) 6 months after the treatment has finished. Smoking abstinence is defined as the self-reported continuous smoking cessation (≤ 5 cigarettes since the start date of their last attempt to quit) validated by the exhaled carbon monoxide test (< 10 ppm of carbon monoxide) [46]. Food insecurity is categorised into four groups: food security; mild food insecurity; moderate food insecurity; and severe food insecurity according to the Food and Agriculture Organization of the United Nations [21].

Secondary outcomes at one and 6 months post-intervention include the point prevalence of smoking abstinence, the mean number of cigarettes smoked per day, the mean number of affirmative responses on the FIES, and the health-related quality of life scores.

Time perspective will be investigated as moderator.

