### Strengths and limitations

One of the most important strengths of this study is the stakeholder engagement within the food pantry setting. Over the last few years, food pantries in Germany have broadened their mandate from solely distributing food to establishing central meeting points where clients are able to drink coffee, eat snacks, and meet peers while waiting to receive their food [58]. As revealed by a previous study, the majority of users regularly visit a food pantry at least four times per month for more than 1 year [11]. This makes food pantries an ideal setting for interventions aimed at a population group that is otherwise hard to reach. By providing the smoking cessation program in the same place as the food pantry, demands and barriers will be minimised for the participants.

This study is innovative as it adapts an already existing well-established smoking cessation program to the specific needs of food pantry users. Furthermore, this study is needed to address health inequalities within an underserved population group.

The “Tafel” food pantries are strongly connected and collaborate under the federal association called “Tafel Deutschland” [54]. If the intervention is effective, this network will enable the expansion of the intervention throughout the country.

Despite the thoroughly planned design, this study is not without limitations. For instance, there is the possibility of bias due to the unblinded design of the study after the baseline assessment. Participants in the control group might be disappointed upon the realisation that they have to wait for the intervention, potentially leading to attrition bias.

In addition, designs using waiting list controls have been criticised as they may overestimate intervention effects [59]. Participants, in particular those who are ready to change, may stop or delay their efforts to change during the waiting period [60]. Using an active control could prevent potential nocebo effects but an equivalent smoking cessation program appropriate for food pantry users, or even low-income people in general, was not available*.* In addition to the lack of an appropriate program for comparison, the program implementation is very complex and expensive which made the researchers decide on a waiting list control group.

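### Carrying the baseline forward scores every missing 6-month food security result as not improved, which is not reliably conservative if dropout differs between arms

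*Protocol article*

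**What the plan says.** The Statistical analyses section of the protocol article sets an intention-to-treat analysis, "therefore including all participants irrespective of any dropouts after the baseline assessment", and one rule for missing data: "Missing values among the intention-to-treat population will be imputed using the baseline observation carried forward technique". No outcome is exempted, and no other imputation method or sensitivity analysis is named.

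Under Outcomes, the second primary outcome is "increased food security level (the percentage of participants with an improved food security level) 6 months after the treatment has finished". The hypothesis is directional: "The percentage of participants with an improved food security level 6 months after the treatment will be higher in the intervention condition". It is tested "using the chi-square test adjusted for intraclass correlation within clusters", and mixed logistic models are also planned. Hypothesis 3 uses a structural equation model in which abstinence predicts food security improvement (path B).

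Two other places bear on missing data. Strengths and limitations warns: "Participants in the control group might be disappointed upon the realisation that they have to wait for the intervention, potentially leading to attrition bias". Study procedure provides a second route to follow-up data: "Participants who cannot be reached at the food pantry will receive the follow-up questionnaires by post".

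**The concern.** For abstinence, treating a missing participant as a smoker is the usual convention. For food security the same rule does something different. The outcome is a change from baseline, so a carried-forward baseline level can never be an improvement. Every participant without a 6-month FIES becomes a failure, including those seen at 1 month, when the FIES is also collected for the secondary outcomes.

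Such a rule is often thought cautious. It is cautious only if the arms lose similar numbers. If the waiting-list arm loses more, its improvement rate is pushed down further and the difference moves towards hypothesis 2. Participants and staff know the allocation after baseline, so unequal loss is a realistic possibility. At stake is a primary hypothesis that could be declared positive partly because of who failed to return.

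Hypothesis 3 has a related problem. Someone lost at 6 months is coded both as smoking and as not improved, and that ties the two variables together whether or not one affects the other.

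**Working it through.** **Inputs from the article.** 416 participants in 32 pantries, 13 per pantry, hence 208 per arm; intraclass correlation 0.02; cessation 10% versus 3%; 5% significance, sidedness not stated.

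**The plan's own figure.** The design effect is 1 + (13 − 1) × 0.02 = 1.24. With t quantiles on 2(k − 1) degrees of freedom, clusters per arm are

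k = (t₀.₉₅ + t₀.₈₀)² × (0.10 × 0.90 + 0.03 × 0.97) × 1.24 / (13 × 0.07²) = 15.09,

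rounded up to 16 per arm, or 32 in total. This matches the stated 32, but only with a one-sided 5% test; the two-sided variants tried gave 38 to 44. Sidedness does not affect the present point, but both forms are shown below because the article does not settle it.

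**Assumed inputs.** The article gives no improvement or dropout rate. I take a true improvement rate p of 10 to 40%, the same in both arms; several pairs of attrition rates d_I (intervention) and d_C (control); missingness unrelated to outcome; and the 0.02 correlation applied to food security as well.

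**Bias under no true effect.** The analysed rates are p(1 − d_I) and p(1 − d_C), so the spurious difference is p(d_C − d_I). Everyone stays in the denominator, so the effective size per arm is 208 / 1.24 = 167.7. Example: with p = 20% and attrition of 20% versus 30%, the rates are 16% and 14%, a difference of 2.0 points. The pooled standard error is √(0.15 × 0.85 × 2 / 167.7) = 0.039, and the chance of a significant result favouring the intervention is 7.4%.

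Each cell gives the spurious points, then the chance of a false significant benefit with a two-sided test (nominal 2.5% in that direction), then with a one-sided test (nominal 5%).

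| p | 20% vs 25% | 20% vs 30% | 20% vs 40% |
|---|---|---|---|
| 10% | 0.5; 3.7%; 7.0% | 1.0; 5.3%; 9.7% | 2.0; 10.7%; 17.7% |
| 20% | 1.0; 4.4%; 8.2% | 2.0; 7.4%; 12.9% | 4.0; 18%; 27.8% |
| 30% | 1.5; 5.1%; 9.3% | 3.0; 9.6%; 16.2% | 6.0; 27.0%; 38.3% |
| 40% | 2.0; 5.9%; 10.6% | 4.0; 12.3%; 19.9% | 8.0; 37.1%; 49.5% |

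**Boundary cases.**
- Equal attrition: 0 points, and two-sided type I error of 5.0%.
- Reversed attrition (30% intervention, 20% control): −1.0 to −4.0 points, against the intervention.
- If dropouts improve at rate q rather than p, the bias is q(d_C − d_I). It vanishes when q = 0.
- With a real effect of 25% versus 20%, equal attrition of 20% shrinks 5 points to 0.25 × 0.80 − 0.20 × 0.80 = 4.0. Attrition of 20% versus 30% inflates it to 0.25 × 0.80 − 0.20 × 0.70 = 6.0.
- Using observed data, or imputation under missing at random within arm, the null scenarios give an expected difference of 0 and a two-sided error of 5.0%.

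**Path B.** Suppose 30% are missing on both outcomes. Among completers, 10% are abstinent and 30% improved, independently. After the rule, abstainers are all completers and 30% of them improved. Non-abstainers make up 1 − 0.70 × 0.10 = 0.93 of the sample, of whom 0.70 × 0.90 × 0.30 = 0.189 improved, so their rate is 0.189 / 0.93 = 20.3%. A gap of 9.7 points appears where none exists, without any difference between arms. If the missing food security values are instead filled at the completers' rate, non-abstainers reach (0.189 + 0.30 × 0.30) / 0.93 = 30%, and the gap is 0.

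**The case against.** A reader might infer that the protocol expects more dropout among controls and that a false benefit therefore follows. The text does not support this. The limitations passage speaks only of what might happen, gives no rate, and does not link attrition to either primary outcome. Loss could also run the other way: controls receive the program only after the last assessment, which is a reason to stay in contact, and the voucher raffle for those completing follow-up applies to both arms.

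The postal questionnaire can recover the FIES itself, so missingness on this outcome may be modest. In the earlier German study about 70% of pantry users were food insecure. The remaining 30% or so could not improve, and the rule codes them correctly. On that basis an overall p of 30% means about 43% of insecure participants improving without any treatment effect (0.30 / 0.70), and 40% means about 57% (0.40 / 0.70). The upper rows of the table are therefore generous. These points limit the size. They do not make the rule conservative.

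Two further inferences should be resisted. One is that 4.9 points (7 × 0.70) is the largest possible true effect on food security. That assumes improvement comes only through full cessation, whereas smoking less could also free money, and the 70% describes all pantry users rather than smokers. The other is that a baseline carbon monoxide reading would be carried forward to validate a postal self-report, possible in principle because eligibility covers anyone "who reported smoking at least one cigarette or cigarillo per day". That needs the rule to be applied to carbon monoxide as a separate variable, which the article does not say. Applied to the outcome as defined, it yields a smoker.

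Finally, the alternative is not free of assumptions: disappointment-driven dropout may not be missing at random.

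**Conclusion.** The point holds in conditional form. The article fixes a single imputation rule that, for food security improvement, is neutral under the null only when attrition is equal or when no dropout would have improved. With assumed improvement of 10 to 40% and attrition of 20% versus 25% up to 20% versus 30%, the artefact is about 0.5 to 4 points, and a false significant benefit occurs about 4 to 12% of the time instead of 2.5% (two-sided). Wider gaps give more.

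For scale, the assumed 7-point cessation difference would move food security through quitting by 1.4 points if 20% of the extra quitters improved (7 × 0.20), and by 7 points if all did. An artefact of 2 to 4 points is therefore material.

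The distortion of path B does not depend on unequal attrition, only on people being lost on both outcomes. I rate this should-fix, with moderate confidence, because the rates are assumptions and the direction of any attrition difference is unknown.

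**What to change.** Before any analysis by arm, replace the general rule with one stated by outcome:

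- **Abstinence:** keep missing as smoking, applied to the outcome as a whole and not to its components.
- **Food security and the other non-abstinence outcomes:** make the primary analysis either multilevel multiple imputation (pantry, arm, baseline and 1-month values in the imputation model) or a likelihood-based mixed model using all three assessments. Under imputation, impute the 6-month value and derive improvement afterwards, and carry the same values into the mediation model.
- **Sensitivity:** retain baseline carried forward, and add delta-adjusted analyses that let dropouts do worse than missing at random implies, with different shifts by arm.

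The cost is a revised paragraph and modest programming, with no new data. The mixed logistic models already planned can be pooled across imputations. The downside is that the primary analysis then rests on missing at random, which dropout from disappointment could violate; the delta analyses show how far the conclusion depends on it.
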